Besides these instruments which are established in palliative care, we will use Goal Attainment Scaling (GAS) [19], which originates in the mental health field, for use in palliative care. GAS is a procedure to formulate individualized goals and objectively evaluate them. Contrary to standardized pre-formulated assessment tools each GAS chart is individually created by an interview process of a health professional and the patient [20]. Alternatively, persons close can assist or charts can be created within the team. The individualization is not only referring to the goal, but also to the indicator chosen whereby a five-point scale ranging from − 2 to + 2 is built to objectively rate whether the actually attained level refers to the expected level of achievement (score ‘0’) or to a much or somewhat better (score ‘+ 2’ or ‘+ 1’) or much or somewhat worse (score ‘-2’ or ‘-1’) level. GAS is meanwhile established in psychology, physical therapy, and occupational rehabilitation, for example in neurology, geriatric medicine, or chronic pain rehabilitation. Using GAS could enrich palliative care as a valuable supplementary tool to meet the requirements of individualization. Although goals are already addressed, GAS advances the process of goal setting, prioritization, pooling of resources, and evaluation more systematically. Moreover, the joint process between the health professional and the patient facilitates communication on realistic perceptions and can help to identify further needs. This also pertains to the meetings within the team. By the transformation of the scores of individually set goals into a single, aggregated t-score [19], GAS visualizes the beneficial effect of SOPC and allows for objective comparison across patients with very varying conditions. To validate GAS for use in palliative care, practicability, content-validity, construct-validity, reliability, and sensitivity to change will be evaluated by individual case assessments in combination with Consumer Quality-indices PC (CQ-indices PC) and Sense of Security (SEC), see also below. To our knowledge, there have been no studies evaluating and reporting the use of GAS within a palliative care setting. For the piloting of the instruments starting in May 2018, five to seven SOPC teams will be chosen sequentially on a voluntarily basis, taking into account criteria to reach a broad diversity, regarding regional differences and the organizational structure of the teams. Participating teams, consisting of 6–20 professionals each, will be trained in study procedures and practical application of instruments in daily routine. The teams will be supervised for a period of 2-months of participation.

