To test psychometric properties of both instruments, we will conduct a field test among *n* = 100–150 cases. Study participants (patients or their unpaid caregivers/relatives or their bereaved ones) have to be at least 18 years old, provided care by a SOPC team, fluent in German to complete the questionnaire and willing to participate in our study. Descriptive analyses (skewness of distributions, floor−/ceiling-effects, missing values, high correlation in item-pairs, low relevance for patients and persons close to them) will indicate problematic items.

To assess internal consistency, we calculate Cronbach’s alpha among scales and sub-scales. For all cases, we will combine data gathered with both measure sets tested within this study with additional data routinely documented for each patient included in SOPC in Hesse. In order to assess construct validity, we will evaluate pre-specified assumptions of correlations of the different constructs within our data [29]. For example: we assume that a change in the symptom burden as measured by IPOS will correlate with the patient’s assessment of the quality of care regarding his or her physical wellbeing as measured by the CQ-index PC. Due to the fact, that we will test a series of assumptions within a relatively small sample size, we will not perform formal statistical hypothesis testing, which would be prone to multiple testing. Instead of *p*-values we will provide correlations coefficients and the respective 95% confidence intervals. For SEC, the development studies showed three-component structures of both, the patient and the relatives version [23, 24]. We will use principal component analysis to confirm these structures.

As there is no accepted instrument as reference standard for measuring criterion validity, individual case assessments by an expert panel will serve as reference standard. All obtainable data of a patient case will be included. The overall quality of care will be rated by an independent expert panel, consisting of at least one member of the research team and one palliative care-expert. A six-point Likert-type scale ranging from 1 (very good quality) to 6 (unsatisfactory quality) will be applied; this rating will serve as reference standard for the CQ-indices PC.

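### The expert-panel grade that serves as reference standard for the CQ-indices PC may draw on the case's own CQ-index responses, which would inflate the criterion-validity correlation

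*Protocol article*

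**What the plan says.** The relevant text is in the protocol article, section on the additional set of measures (adaptation, validation and evaluation).

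- No accepted instrument is available as a criterion, so "individual case assessments by an expert panel will serve as reference standard".
- On the panel's material: "All obtainable data of a patient case will be included".
- On its membership: an "independent expert panel, consisting of at least one member of the research team and one palliative care-expert".
- On the scale: "A six-point Likert-type scale ranging from 1 (very good quality) to 6 (unsatisfactory quality) will be applied".
- On the use of the grade: "this rating will serve as reference standard for the CQ-indices PC".

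The preceding paragraph of that section describes the study data: "For all cases, we will combine data gathered with both measure sets tested within this study with additional data routinely documented". Table 2 places the CQ-index (patient and bereaved versions) in the additional set, and Table 1 places Goal Attainment Scaling (GAS) in the core set.

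The article nowhere says that the CQ-index responses are kept from the panel, or that the grade is fixed before they are seen.

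**The concern.** A reference standard should be established without knowledge of the instrument it is used to judge. Here the rule for the panel's material is all-inclusive, and the CQ-index form is among the data collected for the case. A panel that reads how the patient or bereaved person rated the care, and takes it into account, will agree with that rating partly by construction. This is incorporation bias.

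The reported coefficient could then not distinguish a CQ-derived tool that tracks quality of care from a panel that read the form. The panel grade is the only external criterion the article names for the CQ-indices PC, so no second criterion is available as a check. Once the grades have been given unmasked, the same panel cannot undo the exposure.

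**Working it through.** The article gives no figure for this comparison, so there is none to reproduce. The check has two parts.

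**1. Does the text allow the overlap?**

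- Material for the grade: all data that can be obtained on the case, with no exception stated.
- Data collected on the case: both measure sets plus routine documentation. The CQ-index is in the additional set (Table 2).
- Role of the grade: reference standard for the CQ-indices PC.
- Masking of the panel to CQ-index responses: none stated.

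Followed as written, the rule lets the CQ-index responses into the grade. When the panel meets is not stated. This matters for the bereaved version, which is completed 6 to 24 weeks after death and might not yet exist when a case is graded.

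**2. Direction and possible size**

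Inputs:

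- Field-test size 100 to 150 cases (same section).
- ρ, the correlation between the CQ score and the grade the panel would give without it. Assumed 0 and 0.30.
- w, the weight of the CQ score in the actual grade. Assumed 0.2 to 0.4.
- A product-moment correlation, with the six-point grade reversed so that higher means better. This is also an assumption: the article promises coefficients with 95% confidence intervals for construct validity and names no statistic for criterion validity.

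Let Q be the standardised CQ score and E the standardised judgement formed without it. The grade is (1−w)E + wQ, and the observed correlation is

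r = [(1−w)ρ + w] / √[(1−w)² + w² + 2w(1−w)ρ].

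| ρ | w | Numerator | Denominator | Observed r |
|---|---|---|---|---|
| 0 | 0.2 | 0.20 | √0.680 = 0.825 | 0.24 |
| 0 | 0.4 | 0.40 | √0.520 = 0.721 | 0.55 |
| 0.30 | 0.2 | 0.44 | √0.776 = 0.881 | 0.50 |
| 0.30 | 0.4 | 0.58 | √0.664 = 0.815 | 0.71 |

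*Direction.* The numerator equals ρ + w(1−ρ), which exceeds ρ for any w > 0 and ρ < 1. The squared denominator equals 1 − 2w(1−w)(1−ρ), which is at most 1. So for ρ from 0 up to below 1, any positive weight raises the correlation.

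*Six-point scale.* A simulation that rounded the grade to six points, with w = 0.2, gave 0.23 for ρ = 0 and 0.48 for ρ = 0.30. The pattern is unchanged.

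*Sample size.* The sample size n does not enter the formula for r; it only narrows the interval around the shifted value. By the Fisher z method, z = atanh(r) ± 1.96/√(n−3):

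- r = 0.24: 95% CI 0.05 to 0.42 at n = 100, and 0.08 to 0.39 at n = 150, although ρ is 0.
- A masked grade with ρ = 0.30 has an expected interval of 0.11 to 0.47 at n = 100 and 0.15 to 0.44 at n = 150. The value of 0.50 seen at w = 0.2 lies above both upper limits.

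*After the fix.* With w = 0 the formula returns r = ρ.

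**The case against.** The strongest reply is that the article never lists the contents of the panel file. The sentence on combining both measure sets belongs to the paragraph before and sits between internal consistency and construct validity, so it describes the study data rather than what the panel reads. The rule on obtainable data is one general sentence in a condensed article that also calls the panel independent.

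Part of this stands. That the panel will have the CQ-index form in front of it is the literal reading, not a stated fact, and the point must be put conditionally. But the article is not silent: it makes an all-inclusive statement about the panel's material. Nor does independence answer the point. The panel includes someone from the research team, and independence from the care team would still not be masking to the scores.

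The size is also hypothetical. The weights are assumed, the article sets no threshold for validity, and it avoids formal testing in its construct-validity analysis. An interval excluding zero is therefore no decision rule here, and it does not follow that a worthless tool would be declared valid.

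A reader might infer three stronger claims that the article does not support:

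- **GAS.** The section on the core set says that validation of GAS "will be evaluated by individual case assessments in combination with Consumer Quality-indices PC (CQ-indices PC) and Sense of Security (SEC"). But the properties listed for GAS do not include criterion validity, and the panel grade is named as reference standard only for the CQ-indices PC.
- **Sense of Security (SEC).** No passage uses the panel grade as the reference for SEC. Having SEC scores in the file does not put the CQ-index into its own reference.
- **Nationwide use.** The Discussion makes this depend on feasibility, utility and acceptance as well as validity and reliability. The CQ-derived tool also has content ratings, cognitive pretesting, internal consistency and construct correlations behind it.

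**Conclusion.** The point holds for the CQ-indices PC. As written, the rule for the panel's material admits the case's own CQ-index responses into their reference standard, and nothing in the article prevents it. The criterion-validity correlation is inflated to the extent that the panel gives those responses positive weight, and neither more cases nor confidence intervals in place of p-values correct this.

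The direction rests on the wording and on that positive weight. The size cannot be derived from the documents: the rises from 0 to 0.24–0.55 and from 0.30 to 0.50–0.71 apply only under the assumed weights of 0.2 to 0.4. The conclusion does not extend to SEC. It would extend to GAS only if the panel grade were also used to validate GAS.

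**What to change.** In the section on the additional set of measures, replace the sentence on the panel's material with wording such as: *The panel rates each case on all available data other than that case's CQ-index responses (patient and bereaved versions); its grade is recorded and locked before those responses are seen.* State that only this masked grade is the reference standard for the CQ-indices PC. A second grade given after unmasking may be kept as description.

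SEC, the Integrated Palliative Outcome Scale, Views on Care, the Zarit Burden Interview and GAS may all stay in the file for the CQ analysis, so the patient and caregiver perspective is still represented. Only if the panel grade is also used to validate GAS should GAS scores be withheld for that grade as well. This would be more laborious, because Table 1 has GAS applied at every appointment.

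The cost for the CQ-indices PC is leaving one instrument's forms out of the panel file and recording when the grade is locked. No additional patients or data are needed. The panel grades with slightly less information, and the reported correlation will probably be lower.

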## Methods and design

The ELSAH-study takes place in the state of Hesse, Germany. There are 22 SOPC teams, who provide their services to the approximately 6 million inhabitants. The teams are organized within the Professional Association of SOPC of Hesse (Fachverband SAPV Hessen e.V. [10]), which has the lead of the ELSAH research cooperation. Within this association, each team agreed on sharing a common quality management system and on developing a common documentation system.

Each team provides standardized and non-standardized minimum data on each case on an annual basis with 6.500 cases in 2015. These structures facilitate the recruitment of study participants (professionals and those affected) and the planned statewide implementation and evaluation of the quality instrument set.

The study started in April 2017 and will end in March 2020; the recruitment of participants for the entire project started in May 2017 and will end in December 2019.

The study is divided in two phases: a preparation phase and a main study phase. The preparation phase has been finished and was the prerequisite for choosing a set of preliminary instruments. Aims of the main study are to pilot, adopt, test and implement the instruments within the SOPC setting. Figure 1 shows the study work flow.

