#### Additional set of measures: adaptation, validation and evaluation

The additional set of measures includes the Consumer Quality Indices Palliative Care (CQ-indices PC) [21, 22] and the Sense of Security in Care (SEC) [23, 24]. The methodological approach is basically the same for both of the instruments but differs slightly in the following way: regarding the SEC we aim to validate a German version. With respect to the CQ-indices PC our primary aim is not to validate the original questionnaires. The CQ-indices PC were developed to assess a broad range of health services. However, we will focus on a very specific setting (SOPC). Moreover, some items of CQ-indices PC are irrelevant in the German setting, e.g. in the original version patients are asked if health professionals provide information on euthanasia which is strictly forbidden in Germany. Therefore, CQ-indices PC will be used as a pool of items to derive a tool for the specific setting of SOPC.

German health professionals fluent in Dutch or Swedish language will translate all questionnaires into German. Study team members will adapt the wording of the questionnaires according to cross-cultural and setting-specific factors.

Adult SOPC patients, their unpaid caregivers/relatives and bereaved ones (*n* = 5–10 each) are encouraged for a cognitive-pretesting of the questionnaires [25, 26], including ‘think aloud’ and probing techniques to assess practicability and to identify unclear verbalization [27, 28].

To assess content validity of the items of the CQ-indies PC, professionals of all SOPC teams in Hesse and national palliative care experts will be invited to rate the appropriateness of all items to assess the quality of care within the setting of SOPC. For this purpose, a four-grade likert-type scale will be used.

Based on the results, item reduction (CQ-indices PC) and re-wording (CQ-indices PC and SEC) will be considered. Removal of an item will be considered if the median of the professionals’ rating is below the three. Complementary, participants will be asked to suggest relevant additional items. The resulting version of SEC will be translated back into the original language and potential differences will be discussed with the authors. For the CQ-indices PC, backward translation is not mandatory due to the fact that we do not aim for an one-to-one adaptation of the original instrument.

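### The expert panel that supplies the reference standard for the CQ-indices PC is called independent but must include a research-team member, and it is not kept from seeing the CQ answers

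*Protocol article*

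**What the plan says.** The relevant text is in the Protocol article, section *Additional set of measures: adaptation, validation and evaluation*.

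- **Purpose.** "As there is no accepted instrument as reference standard for measuring criterion validity, individual case assessments by an expert panel will serve as reference standard".
- **Material.** "All obtainable data of a patient case will be included".
- **Panel.** Overall quality of care is to be "rated by an independent expert panel, consisting of at least one member of the research team and one palliative care-expert".
- **Scale and use.** "A six-point Likert-type scale ranging from 1 (very good quality) to 6 (unsatisfactory quality) will be applied", and "this rating will serve as reference standard for the CQ-indices PC".
- **Origin of the tool.** "Study team members will adapt the wording of the questionnaires according to cross-cultural and setting-specific factors". The original questionnaires are not being validated as they stand: "CQ-indices PC will be used as a pool of items to derive a tool for the specific setting of SOPC".

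The section names Cronbach's alpha for the questionnaire scales. For construct validity it names correlation coefficients with 95% confidence intervals. It plans a field test of 100 to 150 cases. It says nothing about agreement between panel members.

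*Methods and design* adds that the professional association in which all 22 care teams are organised is the body "which has the lead of the ELSAH research cooperation".

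**The concern.** A reference standard is useful only if it is obtained separately from the instrument it judges and is itself reasonably reproducible. The wording leaves both in doubt.

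**Independence.** The sentence that calls the panel independent also requires someone from the research team, and that team adapts the instrument under test. With the minimum panel of two, half of the reference can come from the developers' side.

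**Masking.** The panel's material is described without any exclusion. If readers see the CQ answers before grading, the reference partly contains the test, and agreement is pushed upwards.

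**Reproducibility.** A global six-point judgement of care quality carries reader error. If that error is not measured, a modest association cannot be assigned to the tool or to the panel.

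The article concedes that no accepted reference instrument exists, so the criterion-validity result for the CQ tool rests on this grade. The Discussion makes possible nationwide implementation conditional on the instruments showing validity and reliability.

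**Working it through.** The article gives no expected correlation, reliability or sample-size calculation for this analysis, so there is no stated figure to reproduce. The check has two parts.

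**1. The statements side by side**

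| Statement | Consequence |
|---|---|
| Panel is labelled independent | From whom is not stated |
| At least one research-team member sits on it | At least one of a minimum of two readers belongs to the study's own team |
| Study team members adapt the wording; the CQ-indices are an item pool for a new tool | That team helps make the instrument being judged |
| One palliative-care expert sits on it | No condition that the expert is outside the team whose case is graded |
| All obtainable case data are used | The CQ answers are not excluded |

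The label could mean independent of the treating team. That would still not make the panel independent of the tool's developers.

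**2. What unmeasured panel error does to a correlation**

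All reliabilities and true correlations below are assumptions. Using a correlation for criterion validity is also an assumption, since the article names correlations for construct validity. Values are absolute, because 1 is the best grade.

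Formula: observed r = true r × √(panel reliability × tool reliability).

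Ignoring the tool's own error (tool reliability set to 1), with true r = 0.60:
- panel reliability 0.5: 0.60 × √0.5 = 0.42
- panel reliability 0.8: 0.60 × √0.8 = 0.54

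With tool reliability 0.8, two quite different situations give the same expected result:
- true r 0.7, panel reliability 0.4: 0.7 × √(0.4 × 0.8) = 0.40
- true r 0.5, panel reliability 0.8: 0.5 × √(0.8 × 0.8) = 0.40

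Sampling error for an observed 0.40, by Fisher's z (half-width 1.96/√(n − 3) on the z scale):
- n = 100: 95% CI 0.22 to 0.55
- n = 150: 95% CI 0.26 to 0.53

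These intervals describe sampling error only. They cannot separate the two situations; an estimate of reader agreement can help to.

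If the readers grade separately, their mean is also more reliable (Spearman-Brown). A single-reader reliability of 0.5 gives 2 × 0.5/(1 + 0.5) = 0.67 for the mean of two.

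Inflation from seeing the CQ answers works in the opposite direction. Its size cannot be calculated from the article.

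**The case against.** The strongest reply is that this is a condensed article, and that rating procedure, reader assignment and agreement statistics usually sit in a fuller document. That stands: the absence of a kappa or ICC is not a defect in itself.

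Several stronger readings are tempting, and the text does not support them:

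- **One joint grade, with agreement never measured.** This would rest on the singular wording about the rating. Separate grades combined later fit the text equally well.
- **A panel that varies in size from case to case.** The article sets a minimum; it does not describe variation.
- **The research team selects the items by itself.** Item removal is tied to appropriateness ratings by care professionals and national experts, with a median rule. Only the adaptation of wording is expressly given to study team members.
- **The rated teams grade themselves.** The association leads the cooperation, but nothing says that panel members come from it.

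It is also fair to say that independence most naturally means independence from the treating team, and that the composition is disclosed openly. Having helped to word items does not by itself raise their correlation with a care-quality grade. A route is needed, and the open one is access to the CQ answers. Finally, criterion validity is one strand beside content validity, internal consistency and construct validity.

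What survives is the stated composition, the undefined label and the unrestricted case material.

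**Conclusion.** The point holds in a limited form. As written, the panel is not independent of the developers of the tool, and neither the expert's distance from the rated team nor masking to the CQ answers is secured. This follows from the text and needs no assumption.

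The reliability part is conditional. If members' grades are not recorded separately, a modest association is ambiguous between a weak tool and a noisy reference. A strong association would also be open to question if readers had seen the CQ answers. A reader might infer that the criterion result cannot be interpreted at all; that goes too far, because attenuation can be estimated and corrected for once agreement is known.

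The drop from 0.60 to 0.42 or 0.54 illustrates the scale of the problem under assumed reliabilities. It is not a prediction for this study. The change is worth making before grading starts, because separate grades cannot be recovered from a joint one.

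**What to change.** Keep the planned readers and specify:

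1. Each reader records the 1 to 6 grade separately, before any discussion and without sight of the CQ answers.
2. The research-team reader has not worked on the CQ items.
3. The palliative-care expert comes from outside the team whose case is rated.
4. Weighted kappa or an ICC, with its 95% CI, is reported beside the criterion-validity result.

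If this composition cannot be arranged, state from whom the panel is independent, or delete the word.

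Using the mean of the separate grades as the reference, and showing an attenuation-corrected correlation beside the raw one, are optional.

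Cost: a grade column for each reader, one agreement statistic, removal of the CQ answers from the case file before grading, and some coordination in assigning readers. The number of readers per case need not rise, although conditions 2 and 3 narrow who can serve.
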